### **6.1.3. Other secondary outcomes**

Other secondary outcomes are non-generic outcomes specific to a single or two of the CIDs and are listed in the table below (Table A). Unless otherwise specified, the outcomes are changes from baseline to follow-up. Some outcomes are a composite of other outcomes and are grouped together.

**Table A.** Other secondary outcomes with details on how to calculate and measure them.

| Outcome                                                                                                                                                              | Measurement and calculation                                                                                                                                                                                                                                                                                                                                                                                                                                                                                                                                                                                                                                                                                                                                                                                                                                                                                                                                                                                                                                                                                                                          | CID       |
|----------------------------------------------------------------------------------------------------------------------------------------------------------------------|------------------------------------------------------------------------------------------------------------------------------------------------------------------------------------------------------------------------------------------------------------------------------------------------------------------------------------------------------------------------------------------------------------------------------------------------------------------------------------------------------------------------------------------------------------------------------------------------------------------------------------------------------------------------------------------------------------------------------------------------------------------------------------------------------------------------------------------------------------------------------------------------------------------------------------------------------------------------------------------------------------------------------------------------------------------------------------------------------------------------------------------------------|-----------|
| HBI score                                                                                                                                                            | HBI are calculated based on five items. The patient is asked to score item 1-3 based on the previous day [27]: A) General well-being on a scale from 0 to 4 (0=very well, 4=terrible), B) Number of liquid stools per day (the number is included in the final score), C) Abdominal pain on a scale from 0 to 3 (0=none, 1=mild, 2=moderate, 3=severe), D) Abdominal mass (clinical assessment) on a scale from 0 to 3 (0=none, 1=dubious, 2=definite, 3=definite and tender), E) Extra-intestinal complications: arthralgia, uveitis, erythema nodosum, aphthous ulcers, pyoderma gangrenosum, anal fissure, new fistula, abscess (each selected item is awarded 1 point in the final score). The sum of the five items is the score.                                                                                                                                                                                                                                                                                                                                                                                                               | CD        |
| No. of draining fistulas                                                                                                                                             | Clinical examination.                                                                                                                                                                                                                                                                                                                                                                                                                                                                                                                                                                                                                                                                                                                                                                                                                                                                                                                                                                                                                                                                                                                                | CD        |
| Mayo Clinic Score

- “normal mucosal appearance” (findings on endoscopy) (proportion)

- Mayo Clinic response (proportion)
-Partial Mayo Clinic Score | A scoring system for assessment of UC activity. Calculation of the score is based on 4 items [28]: A) Stool frequency per day (0= normal no. of stools for this patient, 1= 1-2 stools more than normal, 2= 3-4 stools more than normal, 3= 5 or more stools more than normal), B) Rectal bleeding (0= no blood seen, 1= Streaks of blood with stool less than half the time, 2= obvious blood with stool most of the time, 3= blood alone passes), C) Findings on endoscopy (0= normal or inactive disease, 1=mild disease (erythema, decreased vascular pattern, mild friability), 2= moderate disease (marked erythema, absent vascular pattern, friability, erosions), 3= severe disease (spontaneous bleeding, ulcers)), and D) Physician’s global assessment (0= normal, 1= mild disease, 2= moderate disease, 3= severe disease). We have decided that endoscopic subscores older than 3 months prior to treatment initiation are excluded.
Response: $\geq 3$ point decrease in Mayo Clinic Score [26] (partial Mayo score: $\geq 2$ point decrease [23]).

The Mayo Clinic Score when omitting the endoscopic subscore (C). | UC        |
| STRIDE remission: Selecting Therapeutic Targets in Inflammatory Bowel Disease (proportion)                                                                           | The STRIDE criteria for remission were developed by a group of IBD experts to achieve international consensus on appropriate evidence-based treatment targets [38]. The agreed upon target for CD is clinical/PRO remission (defined as resolution of abdominal pain and diarrhea/altered bowel habit, addressed in the HBI) and endoscopic remission (defined as resolution of ulceration at ileocolonoscopy) or resolution of findings of inflammation on cross-sectional imaging.

The target for UC is clinical/PRO remission (defined as resolution of rectal bleeding and diarrhea/altered bowel habit, addressed in the Mayo Clinic Score) and endoscopic remission (defined as Mayo endoscopic sub-score of 0-1) [38].                                                                                                                                                                                                                                                                                                                                                                                                                 | CD
UC  |
| Cortico-steroid free remission (proportion)                                                                                                                          | No. of patients reaching either HBI $\leq 4$ or Mayo Clinic score $\leq 2$ without concomitant use of steroids.                                                                                                                                                                                                                                                                                                                                                                                                                                                                                                                                                                                                                                                                                                                                                                                                                                                                                                                                                                                                                                      | CD
UC  |
| Concomitant medication                                                                                                                                               | Change in number from baseline to follow up.                                                                                                                                                                                                                                                                                                                                                                                                                                                                                                                                                                                                                                                                                                                                                                                                                                                                                                                                                                                                                                                                                                         | CD
UC  |
| SCCAI: Simple Clinical Colitis Activity Index                                                                                                                        | SCCAI is a tool developed to measure activity of UC [39]. It consists of six items: A) Bowel frequency (0-3= 0, 4-6= 1, 7-9= 2, $>9= 3$ ), B) Bowel frequency at night (0=0, 1-3= 1, 4-6= 2), C) Urgency of defecation (none= 0, hurry= 1, immediately= 2, incontinence= 3), D) Blood in stool (none= 0, trace= 1, occasionally frank= 2, usually frank= 3), E) General well-being (very well= 0, slightly below par= 1, poor= 2, very poor= 3, terrible= 4), Extra-colonic manifestations (Uveitis, pyoderma gangrenosum, erythema nodosum, arthropathy= 1 per manifestation). The sum of the six items is the total score and ranges from 0-19.                                                                                                                                                                                                                                                                                                                                                                                                                                                                                                    | UC        |
| HAQ-DI: Health Assessment Questionnaire Disability Index

(Composite in                                                                                        | HAQ-DI is a validated PRO instrument for assessing disability in several rheumatic conditions [40]. The questionnaire includes items that assess fine movement of upper extremities, locomotor activities of lower extremities and activities involving both upper and lower extremities during the past week. Furthermore, it also includes items to assess the use of aids and devices or the assistance of another person. Each item is scored from 0 to 3 (0= without any difficulty, 1= with some difficulty, 2= with much                                                                                                                                                                                                                                                                                                                                                                                                                                                                                                                                                                                                                      | RA
PsA |

|                                                                                                               |                                                                                                                                                                                                                                                                                                                                                                                                                                                                                                                                                                                                                                                                                                                                                                                                                          |            |
|---------------------------------------------------------------------------------------------------------------|--------------------------------------------------------------------------------------------------------------------------------------------------------------------------------------------------------------------------------------------------------------------------------------------------------------------------------------------------------------------------------------------------------------------------------------------------------------------------------------------------------------------------------------------------------------------------------------------------------------------------------------------------------------------------------------------------------------------------------------------------------------------------------------------------------------------------|------------|
| ACR20)                                                                                                        | difficulty, 3= unable to do). The items in the questionnaire are divided into 8 functional categories; dressing, rising, eating, walking, hygiene, reach, grip, and usual activities with at least two questions within each category. When calculating the HAQ-DI score, the highest score within a category determines the category score. However, the use of aids, devices or physical assistance increases a score of zero or one to two. The mean of the scores for the 8 categories are the total score (0-3.0). For further details, see reference [40].                                                                                                                                                                                                                                                         |            |
| (DAS)28-CRP: Disease Activity Score                                                                           | DAS28-CRP is a composite measure of disease activity in RA ranging on a scale from 0 to 9.4 [41] [42]. It is calculated using 4 variables (swollen and tender joint counts (SJC and TJC, 0-28), CRP (mg/L) and patient global assessment (PGA, 0-100 mm VAS))[41]:
$DAS28(CRP) = \sqrt{TJC} + 0.28 * \sqrt{SJC} + 0.36 * \ln(CRP + 1) + 0.014 * PGA + 0.96$                                                                                                                                                                                                                                                                                                                                                                                                                                                           | RA
PsA  |
| SDAI:
Simplified Disease Activity Index

- Tender and Swollen joints
-Patient's Global Assessment | SDAI is also a composite measure for monitoring disease activity in RA. The index includes five clinical measures: swollen and tender joint count (0-28), patient global assessment of disease activity (10 cm VAS), provider global assessment of disease activity (10 cm VAS), and CRP (mg/dl). The sum of the five items is the SDAI score [42].
Tender and swollen joint counts + Patient's and Physician's Global Assessment are composites in ACR20.                                                                                                                                                                                                                                                                                                                                                            | RA
PsA  |
| BASMI:
Bath Ankylosing Spondylitis Metrology Index                                                         | BASMI is a clinical measure for spinal mobility. Five clinical measurements are included: 1) lumbar side flexion (cm), 2) tragus to wall distance (cm), 3) lumbar flexion (cm, modified Scober), 4) intermalleolar distance (cm), and 5) cervical rotation (°) [32]. In Believe, a 3-point answer scale (0-2) is used (BASMI 3) based on specific categories corresponding to mild, moderate and severe disease for each of the five measurements. The sum of the five assessments is the BASMI 3 score [32].                                                                                                                                                                                                                                                                                                            | ax-
SpA |
| BASFI:
Bath Ankylosing Spondylitis Functional Index                                                        | BASFI is a self-assessment instrument designed to define and monitor functional ability in patients with Ankylosing Spondylitis (AS). The BASFI comprises 10 questions on which respondents rate the degree of difficulty they have performing different tasks using VAS from 0 (easy) to 100 mm (impossible). The mean of the 10 responses is the BASFI score [43]. BASFI is a composite in the ASAS20 (function).                                                                                                                                                                                                                                                                                                                                                                                                      | ax-
SpA |
| BASDAI:
Bath Ankylosing Spondylitis Disease Activity Index

- Total score for back pain              | BASDAI is also a self-assessment instrument used for evaluation of disease activity in ankylosing spondylitis. It is composed of six questions addressing five symptoms on a VAS (0-100 mm); severity of fatigue, spinal and peripheral joint pain, localized tenderness and morning stiffness (both duration and severity). The mean of the score for the five symptoms (i.e. the average of the two scores relating to morning stiffness is taken) is the BASDAI score [44].
ASAS20: inflammation; mean of BASDAI questions 5 and 6 regarding morning stiffness, pain; spinal joint pain (question 2) [32].                                                                                                                                                                                                         | ax-
SpA |
| Psoriatic arthritis pain                                                                                      | A separate question in the self-administered questionnaire ("how much pain due to your arthritis do you suffer from, the past two days?") on a VAS 0-100 mm.                                                                                                                                                                                                                                                                                                                                                                                                                                                                                                                                                                                                                                                             | PsA
PsO |
| PASI score                                                                                                    | PASI is a standard scoring tool used to measure the severity and extent of psoriasis ranging from 0 to 72. The four main body areas (the head: 10% of total body, the trunk: 20%, the upper extremities: 30% and the lower extremities: 40%) are each evaluated for area of psoriatic involvement with a numerical value from 0-6 corresponding to percentages of involvement in that area [45]. Next, the severity of the psoriatic lesions is evaluated for each body on three factors (erythema, infiltration and desquamation) on a scale from 0-4. For calculation of the PASI [45], for each body area, the sum of severity for these three factors are multiplied with the numerical value of involvement and the percentage of the total body. The sum of the values for the four body areas are the PASI score. | Pso
PsA |
| DLQI:
Dermatology Life Quality Index                                                                       | DLQI is the most frequently used dermatology-specific measure of life quality in clinical trials of skin diseases [46]. It is composed of ten questions concerning the impact of the respondents' skin on different aspects of quality of life over the past week. Each item in the DLQI is scored on a 4-point scale (not relevant/not at all= 0, a little=1, a lot= 2, very much= 3), and the sum of the ten items is the total score (0-30) [46].                                                                                                                                                                                                                                                                                                                                                                     | PsO        |

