### *Primary endpoint*

**Protocol:** The disease specific primary endpoint for UC is a Mayo Clinic Index of 2 or less (with no individual subscore >1).

**SAP:** In cases, where a full Mayo Clinic Index is missing, we will accept a Partial Mayo Clinic Index, which is the Mayo Clinic Index without the endoscopic subscore. However, in these cases, the primary endpoint will be a Partial Mayo Clinic Index of 1 or less [22, 23].

**Rationale:** Some IBD patients refrained from repeated colonoscopies, hence hindering calculation of a full mayo score for UC patients.

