## 6. Analysis

### 6.1. Outcome definitions, measurement and calculation

#### 6.1.1. Primary outcomes

The primary endpoint [2] is the proportion of patients with a clinical response to therapy 14-16 weeks after initiation of treatment with a biological agent. Thus, the primary outcome will be a composite depending on the disease specific definitions of clinical response, defined below:

- CD/Crohn's disease: clinical remission, defined as Harvey-Bradshaw Index (HBI) of 4 or less [25].
- UC/Ulcerative colitis: clinical remission, defined as Mayo Clinic Score of 2 or less (with no individual subscore of >1) [26-28].
- RA/Rheumatoid arthritis: clinical response, defined as at least a 20% improvement according to the criteria of the American College of Rheumatology (ACR20) [29, 30].
- AxSpA/Axial spondyloarthritis: clinical response, defined as at least a 20% improvement according to the Assessment of Spondyloarthritis International Society (ASAS20) [31, 32].
- PsA/Psoriatic arthritis: clinical response, defined as at least a 20% improvement according to the criteria of ACR20 [33].
- PsO/Psoriasis: clinical response, defined as at least a 75% improvement in the Psoriasis Area and Severity Index (PASI 75) [34].

For the measurement and calculation of HBI, Mayo Clinic Score and PASI see table A. ACR20 and ASAS20 are composite outcome measures defined below with composites further explained in table A.

ACR20 is a composite measure developed by the American College of Rheumatology for assessment of improvement of RA patients in clinical trials [30] but also used for assessment of PsA [33]. ACR20 is defined as  $\geq 20\%$  improvement in tender and swollen joint counts and  $\geq 20\%$  improvement in at least three out of the following five measures: 1) pain, 2) patient global assessment, 3) physician global assessment, 4) self-assessed

physical disability and 5) CRP or erythrocyte sedimentation rate. Information for calculation of ACR20 will be extracted from the Simplified Disease Activity Index (SDAI; patients and physicians global assessment and tender and swollen joint count) and the Health Assessment Questionnaire Disability Index (HAQ-DI; disability, see table A), while pain is a separate question in the self-administered questionnaire ("how much pain due to your arthritis do you suffer from, the past two days?") on a VAS 0-100 mm.

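### Steroid-free remission in ulcerative colitis does not use the SAP's own UC remission rule, and no sensitivity analysis isolates the partial-Mayo fallback

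*SAP*

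**What the plan says.** Three places in the SAP bear on UC remission.

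- **6.1.1, Primary outcomes.** The UC component of the primary outcome is "clinical remission, defined as Mayo Clinic Score of 2 or less (with no individual subscore of >1"; the same subscore condition appears in 4.2, where the protocol endpoint is restated as "a Mayo Clinic Index of 2 or less (with no individual subscore >1". No partial-Mayo route is mentioned in 6.1.1.
- **4.2, Protocol deviations, Primary endpoint.** "In cases, where a full Mayo Clinic Index is missing, we will accept a Partial Mayo Clinic Index", and then "the primary endpoint will be a Partial Mayo Clinic Index of 1 or less". The reason given is that "Some IBD patients refrained from repeated colonoscopies, hence hindering calculation of a full mayo score for UC patients".
- **6.1.3, Table A, corticosteroid-free remission (CD and UC).** The calculation column asks for an HBI of 4 or less, or a Mayo score of 2 or less, "without concomitant use of steroids". It has no subscore condition and no partial-Mayo alternative.

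Table A describes the partial score as "The Mayo Clinic Score when omitting the endoscopic subscore (C", which leaves stool frequency, rectal bleeding and physician's global assessment. In the same table, the Mayo response row does give a separate threshold for the partial score.

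**The concern.** An outcome called steroid-free remission would normally be read as remission plus absence of steroids, and so as a subset of remission. For Crohn's disease it is: the HBI threshold in Table A is the one in 6.1.1. For UC it is not, because Table A drops a condition that 6.1.1 imposes. An analyst programming from Table A and one programming from 6.1.1 would classify some UC patients differently.

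Table A also does not say what to do for a UC patient with no follow-up endoscopy. The 4.2 rule gives such a patient a primary outcome, but steroid-free remission is left without a rule, so its denominator is not fixed.

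A second, smaller matter concerns the fallback itself. It switches the rule according to whether the patient had a repeat colonoscopy, which is a post-baseline event. The listed sensitivity analyses would not show whether the primary result depends on that switch.

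**Working it through.** The SAP gives no figure on this point to reproduce. The check lists every possible Mayo profile and applies each rule as written.

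**Inputs.** Four items, each scored 0 to 3 (Table A): stool frequency (A), rectal bleeding (B), endoscopy (C), physician's global assessment (D). This gives 4 × 4 × 4 × 4 = 256 profiles.

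**Step 1. Table A rule against the 6.1.1 rule.**

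- Table A, A+B+C+D ≤ 2: one profile with total 0, four with total 1, and ten with total 2 (six with two items at 1, four with one item at 2). 1 + 4 + 10 = 15.
- 6.1.1, the same total with no item above 1: 1 + 4 + 6 = 11.
- Difference: 15 − 11 = 4. Each has one item at 2 and the rest at 0. By the Table A anchors, one of these is visible blood with most stools and another is moderate disease on endoscopy. All four count as steroid-free remission (if no steroids are used) and fail the SAP's UC remission rule.

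**Step 2. Patients without endoscopy.** A primary responder under 4.2 has A+B+D of 0 or 1. The unseen item C can be 0 to 3, so the full total could be anywhere from 0 to 3 (partial score 0) or from 1 to 4 (partial score 1). Whether it is 2 or less cannot be determined, so Table A gives no status.

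**Step 3. The 6.1.1 rule against the 4.2 fallback.**

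- Fallback, A+B+D ≤ 1 with any C: (1 + 3) × 4 = 16 profiles.
- Of these, C = 0 or 1 also meets the full rule: 4 × 2 = 8. With C = 2 or 3 it does not: 4 × 2 = 8.
- The full rule is met but the fallback is not when two of A, B and D are 1 and C = 0: 3 profiles. Check: 8 + 3 = 11.
- The rules disagree on 8 + 3 = 11 of the 8 + 8 + 3 = 19 profiles that meet either.

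Eight profiles are therefore responders only if endoscopy is skipped, and three only if it is done.

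**Step 4. Sensitivity analyses (6.4).** The numbered list is complete case, non-responder imputation, per protocol, and unmodified eligibility; the text adds best- and worst-case filling of missing outcomes. None separates UC patients scored by full Mayo from those scored by partial Mayo.

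These counts show which classifications are possible. Profiles are not equally likely, so the counts are not shares of patients.

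**The case against.** The strongest reply is that the partial-Mayo rule is no rival definition. It is a declared deviation, with a trigger, a threshold, cited support and a reason, in the section where the SAP says deviations are explained. That stands. A reader might infer that the SAP holds several competing definitions of UC remission, but the documents do not support this: 4.2 is a fallback to 6.1.1, and its absence from 6.1.1 is an editorial gap. STRIDE remission is a separately named outcome and no conflict either.

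A reader might also infer that the UC row of Table 2, labelled only with Mayo ≤2, will report something other than the UC part of the composite. That does not hold. The row sits under the primary outcome's sub-components in an empty table shell, next to similarly short labels, and nothing tells the analyst to compute a different variable.

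It is further fair to say that dropping the fallback would not remove the dependence on endoscopy. Those patients would become missing outcomes, to be imputed or counted as non-responders.

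Two replies go less far. Table A might be shorthand, but the wording stands in the column for measurement and calculation, and the nearby Mayo response row spells out its partial-score alternative. Multiple imputation under 6.3 might fill the missing steroid-free status, but the same patient would then have an observed primary outcome and an imputed remission status, which the SAP should state if it is intended.

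**Conclusion.** The point holds in a narrow form. Table A's UC steroid-free remission rule omits the subscore condition of 6.1.1 and does not say whether the 4.2 fallback applies. As written, 4 of the 15 qualifying score profiles fail the SAP's own remission rule, and primary responders without endoscopy have no defined status. Failing remission here means failing that rule; no judgement is made on which rule is clinically right.

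The fallback is legitimate and disclosed, but it can change a UC patient's primary classification in both directions, and nothing planned isolates its influence.

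The stakes are low. Steroid-free remission is an other-secondary outcome, shown in Appendix Table 1 with a difference and confidence interval but no P value, and it lies outside the Hochberg procedure for key secondary outcomes. A reader might infer that the fallback biases the diet comparison. The SAP does not support that: it gives neither the number of UC patients nor the share without endoscopy, so no effect on the odds ratio can be computed, and bias would arise mainly if endoscopy uptake differed between the dietary groups, for which there is no evidence in the document.

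**What to change.** 1. In Table A, define UC steroid-free remission as the UC primary endpoint met (6.1.1 with the 4.2 substitution) and no concomitant steroids. This makes it a subset of remission and gives every UC patient with a primary outcome a remission status. If the sponsor intends a different rule, Table A should say so and state how patients without endoscopy are handled.
2. Carry the 4.2 substitution into the UC line of 6.1.1, so that the endpoint can be programmed from one place.
3. Add to 6.4 one sensitivity analysis of the primary outcome in which all UC patients are scored by the 4.2 partial-Mayo rule.

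The cost is two edited definitions and one extra model. No new data are needed, because the partial score is made of three of the four items of the full score. The downside is that the extra model rests on a less complete UC measure, since it ignores endoscopy in patients who had it; it should be reported as a check on the substitution, with the primary analysis unchanged.
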